**Baseline requirements**

Participants will be requested:

- to sign the informed consent to participate in the study and to follow the prescribed treatment and lifestyle changes, to provide information on their health status and intervening diseases, and to allow the study officials to contact their treating physicians, to consult clinical notes and to examine blood samples for metabolic, genetic and epigenetic studies, even after the end of the active intervention period
- to fill in a questionnaire on medical history and risk factors (the EPIC-Italy questionnaire)
- to undergo an anthropometric visit (height, weight, waist and hip circumference, blood pressure, body fat and lean mass measured with Tanita impedance device, at baseline and after 1 year)
- to donate a 20 ml blood sample (at baseline and after 1 year)
- to fill in 24h dietary and exercise recall forms (either directly or on the phone) every 2 months in randomly chosen days.

Participants will be informed that they can retire from the study at any moment, but recommended not to do so because it would damage the interpretation of results.

**Randomization**

As soon as all the baseline data are entered, and the eligible participant confirms his/her willingness to go on, a computer system randomly establishes the study groups, balanced for gender and age ( $\leq 65$  years vs.  $>65$  years), and gives instruction to the pharmacy to prepare the drug bottles. The assignment is immediately recorded in the database and not subject to alteration.

**Prescriptions:**

A) 2 tablets per day, one at breakfast (or lunch) and one at dinner, of either metformin (two 850 mg tablets/day) or placebo (two identical tablets) according to the blind assignment. In case of gastrointestinal discomfort occurring after randomization participants will be asked to continue with a single tablet. In our pilot trial such side effect occurred in 10 out of 80 participants: 7 of them stopped taking the pill and 3 continued at half the dose. Subjects stopping taking the pills will be kept in the study, but we will increase the study size by 10% to partly compensate the power loss.

B) participation in the life-style intervention activities. All participants will receive general lifestyle recommendations for the prevention of cancer and cardiovascular diseases, including smoking cessation counselling, and those randomized in the life-style intervention group will be offered to participate to four kitchen courses and will then be invited monthly for lunch or dinner, physical activity sessions, and nutritional counselling to strengthen their commitment over the whole duration of the study. Such a schedule proved to be sufficient to obtain significant reduction of body weight (3 Kg on average after one year) and of MetS parameters in our ongoing randomized trial of lifestyle modification in breast cancer patients.

### Organization

We plan to enrol 25-30 volunteers per week over two years (25 persons per 40 weeks per 2 years = 2,000). Fasting blood samples will be collected between 8 and 9 a.m. Glucose, total and HDL cholesterol, and triglycerides will be immediately measured. We will then prepare 10 aliquots of serum (4 aliquots), plasma (3), red blood cells (1), buffy coat (2), to be preserved at -80°C. The blood collection protocol is compatible with future categorization of genetic and epigenetic variants (we have tested it for miRNA and DNA methylation). For a 10% random sample of participants we will extract immediately the RNA for gene expression studies.

Intervention and control groups will be separately invited every 6 months through SMS messages to refill the tablet bottle and for a short conference. In such occasion we will count the leftover tablets and participants will fill-in a questionnaire on any health events that may have occurred in the interval.

We have developed a very efficient system for communicating to study participants through SMS.

We will use the Milan national Cancer Institute facilities for blood collection and sample storage, laboratories for biochemical, and molecular biology determinations, open air physical exercise, gymnasium, teaching rooms, and dedicated kitchen and restaurant with 60 places for cooking classes and common meals.

### Lifestyle intervention

The intervention aims at increasing physical activity, controlling weight, and promoting nutrient-rich (i.e. 100% RDA for all nutrients) moderately calorie-restricted and protein-restricted low-glycemic index diet. As for physical activity, the goal of the intervention is to achieve and maintain regular participation in a moderate intensity physical activity (approximately 3 to 5 METs) program of 210 minutes over at least 3 days /week (30 min on average per day). During the first four months, one group physical activity teaching session per month will be offered. For self-monitoring and compliance enhancement, study participants will be given a stepcounter and asked to periodically fill-in 24h physical activity diaries. Persons who wish to take up vigorous sports will be encouraged to do so after cardiorespiratory fitness testing. For those who do not progress to more vigorous activity, the focus will be on maintaining moderate intensity activities, such as walking.

To control weight, participants will be encouraged to include whole grains and high-fibre vegetables, which add bulk and volume, in every meal, to choose cooked cereals rather than white bread or dry crackers, to eat vegetables or a soup before eating higher energy foods, to choose fresh fruit rather than juice, to eat nuts at least every other day, and to avoid potatoes, sugary drinks, commercial sweets, white bread and other products based on refined flours, high protein meals, and energy dense industrial foods.

In order to reduce glycaemic and insulinemic response, recommendations will include:

- reducing calorie intake, through the preferred consumptions of highly satiating foods, such as unrefined cereals, legumes and vegetables
- reducing high glycaemic index food, such as refined flours, potatoes, white rice, corn flakes, and high insulinemic foods, such as sugar and milk, preferring instead whole grain rice, barley, millet, oat, spelt, quinoa and buckwheat, legumes (any type including soy products), seasonal vegetables (any type, except potatoes)
- reducing sources of animal saturated fat (red and processed meat, milk and dairy products) preferring instead unrefined vegetable fats, such as olive oil, nuts and oleaginous seeds
- reducing protein intake, mainly animal protein (except fish), down to 10% of total calorie intake
- eat mostly food of plant origin, with a wide variety of seasonal products.

We will teach how to prepare traditional Mediterranean and macrobiotic gastronomic dishes (healthy, satiating, palatable and easy to prepare) based on whole grain cereals, durum wheat pasta, and legumes, seasoned with vegetable sauces and little fat; and competitive cakes and cookies without sugar, milk, butter, and refined flour, using instead dried fruit, such as raisin and apricots, oleaginous seeds, soy milk, cereal flakes and unrefined flour. We will use dietary sources of anti-inflammatory food, such as unrefined cereals, small size oily fish, seaweeds, turmeric, green tea, olive oil, wild berries and other quercetin rich vegetables, such as capers, apples, onion, horseradish, broccoli and other green vegetables, as well as other vegetables rich in phytochemicals that have been shown in vitro to inhibit Akt (which is critical to both cancer and atherothrombotic diseases) and other relevant genetic pathways, such as, genistein, morin, apigenin, delphinidin, luteolin. The principle, however, is to avoid any excess and to guarantee the intake of every potentially preventive bioactive phytochemicals including in the menus a wide variety of seasonal vegetables and fruits. We have recently published a book on the dietary prevention of cancer ([name] and [name], *Prevenire i tumori mangiando con gusto*, Sperling & Kupfer 2009) which include the recipes that will be taught to the lifestyle intervention group.

### Follow-up

We will actively contact the participants for the whole duration of the study, and obtain copy of relevant clinical records. The availability of an efficient regional hospital discharge diagnosis information systems, and of an accessible national death index will make follow-up feasible and complete. The Lombardy region, moreover, is almost completely covered by a network of cancer registries, which will allow to retrieve pathology reports. We will retrieve records for all ArCD but we will first concentrate the analysis on cancer, coronary heart disease, stroke, and diabetes, for which we have already used the above follow-up procedures in several previous studies. For the registration of cancer cases we will follow the rules and definitions of the European Network of Cancer Registries (available at [www.iarc.fr](http://www.iarc.fr)). We will register cancer site, morphology, TNM stage, grade, and, for breast cancer hormonal receptor expression. For the definition of diabetes we will follow the criteria of the American Diabetes Association: a) Symptoms of diabetes plus casual plasma glucose concentration  $\geq 200$  mg/dl (11.1 mmol/l). Casual is defined as any time of day without regard to time since last meal. The classic symptoms of diabetes include polyuria, polydipsia, and unexplained weight loss, or b) FPG  $\geq 126$  mg/dl (7.0 mmol/l), or c) 2-h postload (75 g) glucose  $\geq 200$  mg/dl (11.1 mmol/l). d) In the absence of unequivocal hyperglycemia, these criteria should be confirmed by repeat testing on a different day.

Suspected deaths from Coronary Heart Disease (CHD) and Cerebrovascular Disease (CBVD) will be identified from mortality files when the codes ICD10 I20-I25, R96 and R98 (or E10-E14, I50, I70 in association with I20-I25), or, respectively, the codes I60-I69 (or codes E10-E14, I10-I15, I46, I49, and I70 in association with I60-I69), are reported as underlying cause of death. Fatal CHD and CBVD will be assigned only after verification against hospital discharge and clinical records.

Persons with suspected CHD or CBVD will be identified on hospital discharge forms with ICD9-CM 410-414 codes or procedure codes for coronary revascularization, and, respectively with codes 342, 430-434, 436-438 or procedure codes for carotid revascularization. Clinical records will be retrieved to verify the diagnoses. CHD will be considered verified when acute myocardial infarction, acute coronary syndrome, or coronary revascularization are present, backed up by information on onset symptoms, levels of cardiac enzymes and troponins, and electrocardiogram data coded according to the Minnesota Code. Ischemic thrombotic stroke will be diagnosed when brain infarction is mentioned in the diagnosis and/or confirmed on the basis of imaging exams (computed tomography or magnetic resonance imaging). Hemorrhagic stroke will be diagnosed when cerebral hemorrhage is mentioned in the diagnosis or confirmed by imaging.

For other potentially relevant chronic diseases, such as neurodegenerative diseases, arthritis, gout, fatty liver disease and cirrhosis, gallbladder and kidney stones, autoimmune diseases, which are not formal objectives of the application, we will examine the feasibility to collect reliable and standardized clinical diagnosis in the course of the study.

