### **Study design**

Phase III randomized controlled trial on men and women with MetS to test the hypothesis that comprehensive life-style changes and/or metformin treatment prevent ArCD.

**Design:** 2x2 factorial: 2,000 volunteers will be randomized in four equal groups of 500 each, and allocated to the following treatments:

METFORMIN (1700MG/DAY) + ACTIVE LIFESTYLE INTERVENTION  
PLACEBO + ACTIVE LIFESTYLE INTERVENTION  
METFORMIN (1700 mg/day) alone  
PLACEBO alone

The metformin /placebo component of the study will be double blind.

**Main outcome:** Total incidence of ArCD, including cancer, coronary heart disease, stroke, diabetes. **Secondary outcomes:** changing prevalence of MS and its metabolic and anthropometric components, total mortality, total cancer incidence, incidence of diabetes, cardiovascular diseases, myocardial infarction, stroke. These outcomes have been selected as major objectives because they are fairly easily identifiable on clinical charts according to standardized criteria. Other MetS associated ArCD, however, will be registered in

the follow-up and may eventually contribute to the overall disease burden to be evaluated.

**Recruitment:** Potentially eligible persons will be recruited through cancer screening programmes, general practitioners, clinical units dealing with overweight and metabolic diseases, and the media. Interested persons will be invited to attend conferences in which we will illustrate in detail the study design and its implications. Paper tape measures will be available at the conference to help attendees to check their waist circumference, which is the basic eligibility criteria. Those above the threshold and without any obvious reasons not to be included, will be asked to sign the informed consent form, and will be given an appointment for the first clinic visit and blood sample donation.

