#### Inclusion criteria:

1. waist circumference > 85 cm for women and >100 cm for men
2. age between 55 and 74
3. no diagnosis of cancer in the last 5 years (except skin carcinomas)
4. no diabetes (IDDM and NIDDM),
5. no kidney insufficiency
6. no acute or chronic hepatitis
7. no diagnosis of coronary heart disease, myocardial infarction, stroke, hearth failure
8. no neurodegenerative disease
9. not under treatment with the following drugs:
  - Cimetidine, Ranitidine
  - Sulfamethoxazole + Trimetoprim (Bactrim, Chemitrim, Eusaprim)
  - Nifedipine (Adalat, Nifedidor, Nifasal, Nipin, Fenidina, Euxat, Coral, Citilat)
  - Furosemide (Lasix)
  - Diuretics with K retention: Amiloride (Moduretic), Triamterene, Spironolactone (Aldactone, Uractone, Spirolang)
10. availability to participate in the study for 5 years
11. for women aged 55-69, negative mammography in the last 12 months

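### The stroke rule does not require a new acute event after randomisation, so an old or silent infarct can be counted as an incident stroke

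*Protocol*

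**What the plan says.** The main outcome (Protocol, Study design) is "Total incidence of ArCD, including cancer, coronary heart disease, stroke, diabetes". Cardiovascular disease, myocardial infarction and stroke are also separate secondary outcomes. The event rules are in the Follow-up section.

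- **Non-fatal screening.** Suspected coronary and cerebrovascular cases are found through listed discharge or revascularisation codes, and clinical records are retrieved to verify them.
- **Coronary standard.** "CHD will be considered verified when acute myocardial infarction, acute coronary syndrome, or coronary revascularization are present", and this must be "backed up by information on onset symptoms, levels of cardiac enzymes and troponins" and by coded electrocardiogram data.
- **Stroke standard.** "Ischemic thrombotic stroke will be diagnosed when brain infarction is mentioned in the diagnosis and/or confirmed on the basis of imaging exams". Haemorrhagic stroke is accepted if haemorrhage is mentioned in the diagnosis or confirmed by imaging.
- **Deaths.** Suspected coronary deaths are "identified from mortality files when the codes ICD10 I20-I25, R96 and R98", among others. Then: "Fatal CHD and CBVD will be assigned only after verification against hospital discharge and clinical records".

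On prior disease, the Operative protocol (First meeting, Inclusion criteria) requires "no diagnosis of coronary heart disease, myocardial infarction, stroke, hearth failure". The Exclusion criteria in the Methodology section do not list previous stroke. Baseline requirements include a medical history questionnaire, an anthropometric visit and a blood sample, but no brain imaging.

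**The concern.** An incidence outcome needs a rule that separates a new event from a finding that was already there. The coronary rule does this through its acute-event requirement; the stroke rule has no counterpart. Retrieving the record does not close the gap, because the standard applied to the record is itself a mention in the diagnosis or an image.

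People enter the trial at 55-74 years with metabolic syndrome. Someone with an undiagnosed earlier infarct passes the entry check. If that person is later discharged under a listed code and the infarct appears in the diagnosis or on a scan, the rule allows an incident stroke to be recorded. Its occurrence was settled before randomisation, so neither metformin nor the lifestyle programme can prevent it. Events of this kind fall about equally in all arms and pull the stroke and cardiovascular comparisons towards no difference.

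The death rule raises a smaller question. The search brings in suspected coronary deaths, including R96 and R98, but the protocol does not say how to classify one for which no hospital or other clinical record exists.

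**Working it through.** **Inputs** (Protocol, Analysis, power computations): 175 cancers, 119 major cardiovascular events (not split between infarction and stroke), 219 cases of diabetes; reductions of 25% or 33%; 1,000 v 1,000; alpha 0.05, taken as two-sided. The total is 175 + 119 + 219 = 513, of which 119/513 = 23.2% are cardiovascular.

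**1. The plan's own power.** Control risk p1 = 513/2,000 = 0.2565. With a 25% reduction, p2 = 0.75 × 0.2565 = 0.1924 and the mean risk is 0.2244.

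Power = Φ[(p1 − p2 − 1.96 × s0)/s1], where s0 = √(0.2244 × 0.7756 × 2/1,000) = 0.01866 and s1 = √(p1(1 − p1)/1,000 + p2(1 − p2)/1,000) = 0.01860.

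(0.0641 − 0.0366)/0.0186 = 1.48, so power is 93.1%; for 33% it is 99.6%. With a continuity correction the figures are 92.3% and 99.6%. The protocol's 92% and 99% are reproduced. The figures below use no continuity correction.

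**2. Dilution of the stroke result.** Let f be the share of control-arm counted strokes that are old, and r the true reduction in new strokes. Old strokes are equal in both arms, so the observed reduction is r × (1 − f).

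- f = 0.10: 0.33 × 0.90 = 0.297, about 30%.
- f = 0.20: 0.33 × 0.80 = 0.264, about 26%.

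**3. Effect on wider outcomes.** Because the 119 events are not split, old strokes are added here as a share a of 119 (a different base from f). For all cardiovascular events, the observed risk ratio is (RR + a)/(1 + a). For the composite it is (513 × RR + 119a)/(513 + 119a).

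| a | Composite, true 0.75: RR (power) | Cardiovascular, true 0.75: RR (power) | Cardiovascular, true 0.67: RR (power) |
|---|---|---|---|
| 0 | 0.750 (93.1%) | 0.750 (32.2%) | 0.670 (52.4%) |
| 0.10 | 0.756 (92.6%) | 0.773 (29.5%) | 0.700 (48.2%) |
| 0.20 | 0.761 (92.2%) | 0.792 (27.4%) | 0.725 (44.7%) |

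Example: (384.75 + 23.8)/(513 + 23.8) = 408.55/536.8 = 0.761.

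**4. Unclassified deaths.** Suppose 10-30% of the 119 events were lost equally across arms (assumed; 12-36 events, or 2.3-7.0% of 513). The composite risk ratio stays at 0.750, because numerator and denominator shrink together. Power for a 25% reduction falls from 93.1% to 92.4-90.8%.

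**5. Both together, at the worst assumed values** (30% lost, a = 0.20). Composite: true 0.75 becomes 0.762 with power 89.6%; true 0.67 becomes 0.686 with power 99.1%. Cardiovascular events alone: (0.70 × 0.75 + 0.20)/0.90 = 0.806 with power 19%; (0.70 × 0.67 + 0.20)/0.90 = 0.743 with power 31%.

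**The case against.** The best defence of the stroke rule is that it does not stand alone. A non-fatal case must first carry a listed discharge or carotid procedure code, records are retrieved, diagnosed stroke is an entry bar in the Operative protocol, and the outcome is called incidence. So a reader who infers that any mention of brain infarction counts goes too far: the text says mentioned in the diagnosis, after a code screen. An incidental scan finding in someone admitted for another reason counts only if the discharge carried a listed code. That old strokes will be counted is a possibility the rule leaves open, not something it prescribes. What stands against the defence is that none of these steps tests whether the event is new.

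On deaths, a reader might infer that a coronary death outside hospital can never be confirmed. The protocol does not support this. Clinical records are not confined to hospital records, participants consent to contact with their treating physicians and use of clinical notes (Baseline requirements), and the enzyme and electrocardiogram criteria are not expressly applied to deaths. A reader might also infer that both rules bias towards no effect. Equal under-counting of deaths does not do so (step 4); only falsely added events dilute. A wide search followed by strict confirmation is a defensible trade of sensitivity for specificity, and counting every certificate-coded coronary death unless disproved could itself add diluting false positives.

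Finally, only the metformin/placebo component is described as double blind, which may suggest bias between the lifestyle arms through unequal scanning. Nothing in the protocol shows that scanning would differ.

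**Conclusion.** The stroke rule needs correcting: as written it allows an old or silent infarct under a listed code to count as an incident stroke. At an assumed 10-20% share of old strokes, a true 33% stroke reduction would be seen as about 30-26%. The protocol gives no such share, so these are illustrations. Cardiovascular events alone, already at only 32-52% power, would lose more.

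The primary composite is not seriously threatened. Even the worst assumed pair moves its risk ratio only from 0.750 to 0.762, with power for a 25% reduction going from 93.1% to 89.6%. The case for change rests on the stroke and cardiovascular secondary outcomes and on the low cost.

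The missing classification for coronary deaths without any usable record is a secondary point. It costs events and some precision, and is not a demonstrated bias in the relative effect.

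**What to change.** **Follow-up, stroke rule.** Count a non-fatal stroke only when the retrieved record documents a new acute neurological event of vascular origin with onset after randomisation. Use imaging to classify it as ischaemic or haemorrhagic. Do not count infarction found only on imaging or only in diagnostic codes.

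**Eligibility lists.** Reconcile the Methodology exclusion list with the Operative protocol on previous stroke, so that the population at risk of a first event is defined once.

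**Follow-up, fatal events.** Keep the strict definition for the primary outcome. Add a sentence placing suspected coronary deaths with no hospital or other clinical record, including R96 and R98, in a labelled class of possible coronary deaths, to be included in a sensitivity analysis.

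**Cost.** These are wording changes to be made before events are classified. The discharge data, clinical records and mortality files are already to be obtained, so no new data collection is needed. The downside is that a few true strokes with poor records will be lost.

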### Blood examinations

At baseline and after one year we will examine the metabolic markers of MetS.

Further analysis of insulin, IGF-I, IGF-BPs, PDGF, sex hormone, hsCRP, and inflammatory cytokines, will be carried out in appropriate samples of participants from the third year onward. We will examine baseline and 1-year samples in the same batch. We will study the effect of one year CR, one year MET treatment, or their combination, in subjects with high and low compliance (defined by changes in body weight, waist circumference, and 24h recall diaries). Eventually, we will examine the change in these parameters in people who did or did not develop specific ArCD with a case control design. Changes in epigenetic profiles will be examined in the frame of companion project for which we are seeking independent financial support.

The study team has extensive experience in large-scale prospective cohort studies with biological repository (we are following-up 50,000 persons in Italy), and in dietary intervention studies (we succeeded to randomize 2,000 breast cancer survivors into a lifestyle intervention and control group and we managed to keep a very high dietary compliance of the intervention group).

